# The impact of integrated nutrition-sensitive interventions on nutrition and health of children and women in rural Tanzania: study protocol for a cluster-randomized controlled trial

**DOI:** 10.1186/s40795-018-0238-7

**Published:** 2018-09-06

**Keywords:** Agriculture, Health, Nutrition, Dietary diversity, Children, Women, Extension workers

## Abstract

**Background:**

Nutrition-sensitive interventions such as homestead production of diverse, nutrient-rich foods, coupled with behavior change communication, may have positive effects on the nutritional status and health of rural households engaged in agriculture, particularly among women and young children. Engagement of agriculture and health extension workers in these communities may be an effective way of delivering nutrition-sensitive interventions given the dearth of trained health care providers in many developing countries. This study aims to assess the effects of integrated homestead food production, food consumption and women’s empowerment interventions using a multi-sectoral approach on women’s and child’s health and nutrition.

**Methods:**

This is a cluster-randomized community-based prospective study set in Rufiji district, a rural area in Eastern Tanzania. Ten randomly selected villages within the Rufiji Health and Demographic Surveillance Site (HDSS) in Eastern-Tanzania were paired and randomly assigned to the intervention or control arm. The Rufiji HDSS dataset was used to randomly sample households with women of reproductive age and children 6–36 months. The intervention includes provision of small agricultural inputs, garden training support, and nutrition and health counseling. This is delivered by community health workers and agriculture extension workers through home visits and farmer field schools. There are three time points for data collection: baseline, midline, and endline. Primary outcomes are women’s and children’s dietary diversity, maternal and child anemia status and growth (child stunting, child wasting, women’s BMI, and women and child hemoglobin).

**Discussion:**

This integrated agriculture and nutrition intervention among rural farming households is a simple and innovative solution that may contribute to the reduction of undernutrition and disease burden among women and children in developing countries. Engaging already existing workforce in the community may facilitate sustainability of the intervention package.

**Trial registration:**

ClinicalTrials.gov NCT03311698, Retrospectively registered on October 17, 2017.

## Background

Maternal and child undernutrition remains one of the most challenging health problems in low and middle-income countries (LMICs) [1]. Together they account for more than 10% of the global burden of disease. Nearly half of all child deaths globally, equivalent to 3,000,000 lives lost annually, are attributable to malnutrition. While some improvements in nutritional status have been observed in recent years in many developing countries, including Tanzania, stunting remains a leading form of undernutrition [2]. Undernutrition early in life has devastating consequences to individual health and community development including increased risk of infections, impaired cognitive ability, and reduced school and work performance [3].

Inadequate dietary intake and poor weaning foods in young children, both of which are important causes of undernutrition, are still major problems in many LMICs. Daily meals often lack the diversity needed for supplying essential nutrients for normal growth and prevention of diseases [4, 5]. Other contributors to undernutrition such as diarrhea and recurrent pneumonia are highly prevalent. Suboptimal access to safe water, poor sanitation, and poor health care services also contributes to malnutrition and illness in many rural settings [6]. Thus, it is vital to consider holistic interventions to address maternal and child undernutrition in LMICs for effective and maximum impact in health and economic development.

### Importance of nutrition in women and children

Pregnant and lactating women are among the most vulnerable groups to suffer from undernutrition and micronutrient deficiencies because they have physiologically higher nutrient requirements that are often not met [7]. Women should have a sufficient diet, in terms of both quality and quantity, before and after conception to maintain replete nutrient stores that can sustain themselves and their children. Adequate diet during the preconception period and pregnancy reduces the risk of adverse maternal and newborn outcomes such as low birthweight, stillbirth, preterm, and impaired cognitive and motor development [8, 9].

Similarly, infants and young children have high nutrient requirements due to rapid growth and development [7]. During illness, they experience a heightened demand of nutrients to maintain optimally functional immune systems [10]. This is of particular importance in sub-Saharan Africa due to the high prevalence of infectious diseases, including malaria, HIV and respiratory infections among children under 5 years of age [11].

### Rationale for advancing homestead food production to improve nutrition and health

Investment in the agriculture sector in various countries in Africa has resulted in large increases in staple crops that are typically rich in carbohydrates but poor in micronutrient content [12]. Promoting the agricultural sector with a view of nutrition-sensitive productivity will assist in accelerating nutritional gains in the community, and enhance production of diverse crops that enrich the quality of diets including micronutrient-rich foods [13]. Pathways by which agriculture can influence nutrition include increased home production and household availability of nutrient-rich crops, increased dietary diversification, and increased income and access to food in markets. Financial gains at the household level from agricultural production may have important implications for women who have primary responsibility for food production in many LMICs [14]. This may have direct effects on women’s empowerment through improved access to resources, which may influence their ability to make informed decisions regarding health care and meeting essential needs for their children.

In rural settings, where most households are engaged in smallholder farming, homestead food production (HFP) interventions offer one of the most promising pathways towards improving livelihoods, the diversity of agricultural outputs, food security, and maternal and child nutrition. Small-scale, nutrition-sensitive agricultural interventions equip smallholder farmers with the tools and skills to cultivate home gardens and raise livestock. Home gardens promote production of nutrient-rich fruits and vegetables that can grow well in local conditions. Household members, particularly women, are trained in cultivating the crops and raising livestock [14]. HFP interventions have shown promising increases in food production and dietary diversity [15]. This can improve women and child nutrition directly through consumption, and also indirectly by raising household income, purchasing power for health services, availability of food in markets, and empowerment of women in society.

For maximum health and nutrition impact, HFP interventions should be coupled with behavior change communication campaigns that include nutrition and public health messages, especially among women. This will effectively improve knowledge on the importance of a healthy diet, dietary diversity, and best practices for food preparation, child feeding, and health seeking behavior [16]. However, little is known on the most effective nutrition-sensitive intervention approaches. Furthermore, there is a lack of clarity on which approaches are most effective and feasible for integrating nutrition in agriculture sectors, including within extension services [17].

This study evaluates the effects of integrated nutrition-sensitive interventions on the health and nutrition of children and women in rural Tanzania while exploring the incorporation of existing cadres of agricultural extension workers together with community health workers as a sustainable workforce for providing basic health and nutrition education in rural communities.

## Methods/design

### Study setting

The study is implemented in Rufiji district, Tanzania. Rufiji is one of six districts in the Coast Region of Tanzania, and has a population size of 217,274. It has 94 registered villages and 385 hamlets. The study is operated within the Rufiji Health and Demographic Surveillance Site (RHDSS) where about 20% of households have at least one child under the age of 3 years [18]. The prevalence of stunting and anemia among children under 5 years in Rufiji is 35 and 61% respectively [19]. Its demographic characteristics are representative of rural Tanzania, most adults are subsistence farmers who cultivate staples like maize, rice, cassava, and millet Fig. 1.

**Fig. 1 Fig1:**
[figure not shown]
Map of the study area in Rufiji, Tanzania

### Community-based service delivery

This study engages existing Agriculture Extension Workers (AEWs), Livestock Extension Workers (LEWs) and Community Health Workers (CHWs) to deliver the interventions. AEWs and LEWs are employed by the government to train and support farmers in agriculture and animal husbandry and best practices for increased productivity. CHWs are an existing cadre in many rural settings of Tanzania, but have no formal wages. The project therefore takes advantage of existing cadres of workers who are familiar with their communities.

Typically, each AEW, LEW and CHW works in one village with approximately 400 households. They conduct regular home visits among all households to which they have been assigned providing basic health education, promoting preventive health care services, and supporting best practices in agriculture and livestock production. All three forms of home-based services; health, agriculture and livestock exist in all Rufiji villages.

### Design

This is a 36-month long community-based prospective study carried out in 10 villages. A cluster-randomized design is used to evaluate the effects of the intervention. Data collection take place at three time points, at baseline, midline, and endline. Study activities are summarized in Fig. 2*.*

**Fig. 2 Fig2:**
[figure not shown]
Study activities over study period

Eligibility criteria for households participating in the study are: (i) having a woman of reproductive age (18–49 years) and at least one child 6–36 months of age, (ii) having access to a plot of land or containers where vegetables could be grown, and (iii) provided informed consent.

### Randomization and sampling

The unit of randomization is a village. Ten villages within the Rufiji HDSS were randomly selected and matched based on location, proximity to water, and population size. One village in each matched-pair was randomly assigned to receive the intervention (five villages) and the other to the control group (five villages).

The Rufiji HDSS dataset was used in random sampling of households with at least one woman of reproductive age and at least one child 6–36 months of age in all study villages. We considered a proportional-based representation of households based village size in the random selection of households. Thus, a total of 1006 households were enrolled with a ratio of 1:1 in intervention and control villages (Table 1). Enrolment was initiated on July 2016 and the endline survey is planned for July 2019 Fig. 2.

**Table 1 Tab1:** Sample frame of randomized study villages and households

Intervention villages	Village population size	Number of household with 6–36 months child	Total enrolment
Kibiti A	837	286	170
Mchukwi B	455	129	64
Mgomba North	386	194	134
Umwe North	558	184	71
Umwe South	298	97	65
Total	2534	890	504
Control villages			
Kibiti B	1732	346	206
Mchukwi A	383	86	68
Mgomba South	326	124	104
Ikwiriri South	594	149	84
Ikwiriri Central	230	78	40
Total	3265	783	502

### Sample size

The sample size was pre-determined by the size of HDSS and the logically feasible time frame of 2 years. The number of eligible households which could be enrolled was estimated before (as 1000) to be sufficient for pilot implementation of integrated nutrition-sensitive interventions but no formal sample size calculation was performed.

### Enrolment procedure

Participating households in each study arm were screened, consented, and enrolled. Research assistants (RA) visited and screened sampled households for each study village. RAs introduced the study to the household member and verified participant’s inclusion criteria. For each eligible household, one woman and one child were enrolled in the study after providing informed consent. In case the household has more than one eligible member, simple random sampling technique (lottery method) within each household was used to select one woman. The same technique was used to select one child 6–36 months of age. RAs then proceeded with administration of electronic baseline data collection.

### Description of the interventions

Households in the intervention arm receive: (1) interventions to promote homestead food production and increase agricultural production and food diversity, (2) nutritional counselling, including prevention and management of child malnutrition with a focus on the first 1000 days, locally adapted instructions on the mix and quantity of food suitable for children ages 6–36 months, (3) a health-focused intervention, including information on micronutrient supplementation, integrated management of child illnesses, and safe water, sanitation and hygiene practices (WASH).

Households enrolled in the intervention also receive agricultural inputs such as seeds, fertilizer, and watering cans. Local Agricultural Officers identified six varieties of crops (Africa eggplant, amaranthus, spinach, tomato, okra, and Chinese cabbage) for the study and recommended specific varieties for each intervention village based on growing conditions and village preference. Each participating household in intervention villages receive three varieties of seeds at least three times during the study period.

The behavior change component of the intervention includes information on cultivation of nutrient-rich crop varieties, best practices for home gardening, safe water, sanitation, and hygiene practices (WASH), breastfeeding and complementary feeding, dietary intake and nutrition, and other basic public health messages. AEWs, LEWs and CHWs are trained on topics related to cultivation of nutrient-rich crop varieties and provision of basic public health services to households. This includes encouraging and monitoring the consumption of iron and folate supplements during pregnancy; use of zinc oral rehydration solution for management of diarrhea; promotion of hygienic and sanitary practices at the household level, promotion of preventive health behaviors such as immunization for children; and referral of sick and malnourished children to local health centers for appropriate care.

There are two delivery mechanisms for the intervention: farmer field schools and households visits. Household visits are conducted approximately every 2 weeks. Households receive separate visits from an AEW/LEW or CHW on a rotating schedule. Field schools are also held approximately every 2 weeks and attended by all three types of extension workers.

### Farmer field schools

In collaboration with village and hamlet leaders, AEWs identified one participating household farm in each of four to five hamlets per village to be used as Farmer Field Schools (FFS). Participants within a given hamlet were invited to partake in FFSs. Farmer field schools are open to the public as they also existed in these communities before the intervention took place. Households participating in the intervention are highly encouraged to attend by extension workers. The number of participants attending a FFS typically ranges from 10 to 15, determined by the number of enrolled households per hamlet. Collaboration with village and hamlet leaders ensure that the selected individuals are valued and trusted community members interested in leading fellow farmers. The FFS is designed to (i) illustrate the benefits of innovative agricultural practices to the community, (ii) improve community knowledge about nutritious crops available in the district, (iii) reinforce messages provided by during household visits, (iv) offer a forum for discussion and collaboration between farmers, and (v) empower women with knowledge and skills for increased decision-making at the household level. Model farmers use the demonstration farm as a classroom and hold organized “classes” with other women farmers in their hamlet to illustrate how to become a more productive farmer. The design of FFS enables AEWs to maintain close connections with model farmers, providing them with information about new agricultural technologies and practices as they become available in the district.

### Household visits

AEWs, LEWs and CHWs implement a system of household visits with all enrolled smallholder farming households in the community. All cadres receive basic nutritional, agricultural and maternal and child health training to ensure messages act to reinforce and complement each other. The transmission of the same messages through multiple channels aims to increase their credibility and the probability of longer term adoption of recommended behavioral change. One-on-one meetings with AEWs, LEWs and CHWs through home visit are held biweekly for the purposes of providing maximum amount of information in a feasible manner. Household visits and FFSs are staggered so that farmers receiving the intervention are continually exposed to information through one of these channels.

### Supervision

Extension workers are continuously monitored by the study field manager to sure that the above two main approaches are delivered routinely to participants as outlined in an intervention manual developed by the research team in collaboration with local officials. A list of randomly selected participating households in each intervention village is generated every week and visited by the field manager to conduct monitoring and evaluation of the intervention.

### Data collection

Data are collected by trained interviewers using surveys administered with electronic tablets at three time points, once at baseline, once 12 months after intervention implementation, and once approximately 36 months after intervention implementation. Agricultural practices and primary outcomes are also measured in a random sample of non-participant households in the intervention villages which may assist to inform spillover effect or spread of the intervention. Anthropometric measurements of women and young children take place at three time points. Hemoglobin for women and young children is measured among a subset of the study population at these time points.

### Questionnaires

Questionnaires developed by the research team include socio-demographic and economic data, self-reported recent history of illness, infant and young child feeding, dietary intake, physical activity, agriculture production, food security, and women’s empowerment. Agriculture production data include the area of specified crop production, production quantities, sales of produce and income realized, purchase and use of agriculture inputs, and other operational expenses. Dietary intake is assessed using a food frequency questionnaire.

### Qualitative data collection

Qualitative methods are used to assess the reach of the intervention, opportunities and challenges. Focus group discussions will be conducted with study participants and non-study participants in intervention villages. Key informant interviews will also be conducted with health care providers, extension workers, and village and district officials. Interviews and focus groups aim to ascertain participants’ experiences with the intervention and suggestions for improvement in the delivery and sustainability of the intervention. In addition, the interviews and discussion will also identify bottlenecks and sources of improvement or adaption of homestead agriculture and nutrition interventions in the community.

### Outcomes

The primary outcome for the study is women’s and children’s dietary diversity (number of food groups consumed out of 10) [20, 21]. Secondary outcomes include women’s and children’s anemia status (hemoglobin [Hb] levels < 12 g/dl for non-pregnant women and Hb < 11 g/dl for pregnant women, and Hb < 11 g/dl for children); child growth (weight for age z-score [WAZ], weight for height z-score [WHZ], height for age z-score [HAZ], and mid upper arm circumference [MUAC]); women’s growth (body mass index, and MUAC); early childhood development (Caregiver Reported Early Development Index [CREDI]) [22]; and reach and extent of intervention-promoted practices and behaviors (home gardening and food consumption).

### Data analytical plan

Data will be analyzed based on an intent-to-treat strategy. Data will be classified into three main categories; (i) the primary outcome variables including women and children dietary diversity, (ii) secondary outcomes including women’s and children’s growth and anemia status; and (iii) other covariates including socio-demographic characteristics, village, age, gender, health status, WASH practices, and crop production and practices, and livestock ownership. In addition, standard tools to assess food security (food reserve availability index), dietary diversity in women of reproductive age and children, women empowerment in agriculture index, water and sanitation (WASH) practices as well as household asset index will be incorporated, and aggregate data used to predict vulnerable households.

Height (or length) and weight will be standardized based on 2006 WHO child growth standards to create HAZ, WAZ and WHZ scores. Biological implausible values based on WHO recommended cutoffs at 6 SD will be eliminated.

Generalized linear mixed models with random intercepts and robust standard errors will be used to assess for continuous repeated primary outcomes. Generalized linear mixed models with random intercepts and robust standard errors will be used to assess repeated primary outcomes.

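### Only ten villages are randomised, so robust standard errors without a small-sample correction give about 12–16% type I error, and the article names neither village as the clustering level nor any correction

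*Protocol article*

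**What the plan says.** Under Randomization and sampling: "The unit of randomization is a village". On the matching: "Ten villages within the Rufiji HDSS were randomly selected and matched based on location, proximity to water, and population size". One village of each pair went to each arm, so there are five villages per arm. Table 1 gives enrolments of 40 to 206 households per village, and the text reports that "a total of 1006 households were enrolled with a ratio of 1:1 in intervention and control villages".

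Under Outcomes, the primary outcome is dietary diversity in women and children, a count of food groups out of ten. It is measured at baseline, midline and endline.

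Under Data analytical plan, the only inferential statement for it is "Generalized linear mixed models with random intercepts and robust standard errors will be used to assess repeated primary outcomes". A near-identical sentence on continuous outcomes precedes it. Neither sentence names the level of the intercepts, the level at which the errors are robust, a reference distribution or a use of the pairs. Village appears in that section once, in a list of other covariates. Under Sample size, "no formal sample size calculation was performed". The article gives no alpha, ICC, p-value or interval.

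**The concern.** The sandwich (robust) variance is justified when the number of independent clusters is large. In this trial the independent units for the arm comparison are ten villages, not 1006 households. With so few, the uncorrected sandwich is biased downward, and a normal critical value ignores how poorly it is estimated. Both faults push towards declaring an effect.

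The level also matters. A random intercept in a repeated-measures model is often placed on the person or household. If the robust errors sit there too, clustering by village drops out of the standard error altogether.

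At stake is the main result. The Discussion says that the findings will be taken to policy makers and may lead to scale-up, so a false positive on dietary diversity would carry weight.

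**Working it through.** **Inputs from the article (Table 1).** Intervention: 170, 64, 134, 71, 65 (sum 504). Control: 206, 68, 104, 84, 40 (sum 502). 504 + 502 = 1006, which reproduces the only design figure given. There is no sample size calculation to reproduce.

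**Assumptions, because the article gives none.** Two-sided 5% level, normal outcome, no dropout, ICC 0.01 to 0.10, and no within-pair correlation unless stated.

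**1. Effective number of villages,** (Σm)²/Σm²:
- Intervention: 504²/60,218 = 4.2.
- Control: 502²/66,532 = 3.8.

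**2. Village intercept, village-level robust errors, no correction, normal reference.**
- With equal villages, five per arm, the uncorrected sandwich has expectation (1 − 1/5) = 8/10 of the true variance. The interval is then (1.96/2.31) × √(8/10) = 0.76 of the proper 8-df width, about 24% too narrow. The effective cut-off on a t with 8 df is 1.96 × √0.8 = 1.75, a two-sided error of about 12%.
- Null simulation with the Table 1 sizes: 12.0–13.5% with mixed-model (REML) weights (4,000 runs per setting, Monte Carlo error about 0.5 points); 14.6–15.7% with household weights (20,000 runs); 13.6–16.4% for change from baseline.
- The G/(G−1) correction with household weights still gives 12.9–13.8%. Uncorrected errors referred to t with 8 df (mixed-model weights) give 7.1–8.4%.
- If paired villages correlate at 0.3 or 0.5 (ICC 0.05), the household-weighted figure falls to about 11% or 8%. I checked this with 40,000 null draws per setting. With mixed-model weights m/(1 + mθ), θ = 0.05/0.95, the same draws gave about 8% and 6%.

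**3. Intercepts and robust errors at household level only.** Design effect = 1 + (Σm²/Σm − 1) × ICC, with Σm²/Σm = 126,750/1006 = 126.0. Error ≈ 2[1 − Φ(1.96/√DE)].

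| ICC | Design effect | Error by formula | Error by simulation (20,000 runs) |
|---|---|---|---|
| 0.01 | 2.2 | 19% | 19.5% |
| 0.02 | 3.5 | 29% | 28.8% |
| 0.05 | 7.2 | 47% | 46.3% |
| 0.10 | 13.5 | 59% | 60.0% |

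**4. Change from baseline with intercepts only and no village-level robust error.** The village intercept cancels in the contrast. The error is 4.9% with no village-by-time variance, and 18–57% when that variance is 0.5–5% of the total (assumed).

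**5. Methods that respect ten villages (ICC 0.01–0.10, endline).**
- Village-mean t-test (8 df): 4.0–5.4%.
- Matched-pair t-test (4 df): 4.3–5.5%.
- Village random intercept, model-based error, t with 8 df: 3.9–5.6%.
- Village-level robust error × √(10/8), t with 8 df: 4.8–6.0% (6.4–8.3% for change from baseline).

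**The case against.** The strongest reply is that this is a condensed article. The clustering level, degrees of freedom and small-sample correction commonly go in a full analysis plan, and the quoted sentence is compatible with a sound analysis: a village intercept with 8 df, or a corrected village-level sandwich, holds the endline error at about 4–6%. That stands against three stronger readings.

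- A reader might infer that the trial's p-values and intervals are invalid. The article states none, and the mixed-model class is not invalid in itself.
- A reader might take 19–60% as the size of the problem. It applies only if village is left out of both the intercepts and the robust errors. The text leaves this open. The covariate list sorts variables and does not specify a model, so it does not show that village is left out.
- A reader might say that an intercept-only model must ignore village-by-time variation. Village-level robust errors would absorb it, so the 18–57% range also depends on their absence.

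The pairing is a further mitigation. Villages matched on location, water and size may well correlate, and an unpaired analysis is then less anti-conservative; with mixed-model weights and a correlation of 0.5 it is close to nominal. But the correlation is unknown and cannot be relied on.

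The reply does not remove the point. Robust errors are a stated choice, not a silence. They are the one inferential device named, and their usual uncorrected form fails with ten clusters even when placed at village.

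**Conclusion.** The concern holds in this limited form: the article fixes a large-sample variance method for a ten-village trial and names neither village as the clustering level nor a correction. Placed at village but uncorrected, with a normal reference, it gives about 12–16% error at a nominal 5%, or 2.4 to 3.2 times nominal. About 19–60% is a conditional worst case and not what the text prescribes. The exact sizes rest on the assumed ICC, normality, complete data and no within-pair correlation; pair correlation of 0.3–0.5 lowers the village-level figure to about 8–11% with household weights, and further with mixed-model weights. The downward bias does not depend on the ICC: at village level the error barely moves between 0.01 and 0.10. This is the primary analysis and the error favours a positive finding, so the wording should be changed before the endline data are analysed.

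**What to change.** Replace the sentence with: a mixed model with random effects for village, village-by-visit and household/person, tested with Kenward-Roger or Satterthwaite degrees of freedom tied to the number of villages. The arm contrast that is the main test should be named.

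A t-test on village-level summaries (8 df unpaired) is an acceptable alternative. It is not the same analysis: with villages of 40 to 206 households it weights them differently, so one of the two should be chosen in advance.

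If robust errors are kept, cluster them on village and use the bias-reduced version (CR2) with Satterthwaite degrees of freedom.

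State beforehand whether the matched pairs enter: 4 df if they do, 8 if not. An exact sign-flip test on five pairs cannot go below 2/32 = 0.0625 two-sided, so it is not usable at the 5% level.

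This changes analysis wording only. The cost is precision: the critical value rises from 1.96 to 2.31 (8 df, 18% larger: 2.31/1.96 = 1.18) or 2.78 (4 df, 42% larger: 2.78/1.96 = 1.42). With pairs in the model, the gain from matching may offset part of that.
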